## Materials and Methods

### Trial design

This study is a randomised controlled parallel groups intervention trial (see S1 CONSORT Checklist in S1 File). All United Kingdom (UK) medical schools will be invited to participate (see S3 Appendix 1 in S3 File). Participants will be self-selecting and screened for eligibility based on the criteria that they are a) UK medical student and b) in a year of study that contains a placement of one week or longer. The trial will compare Thumos to a control condition of services as usual (SAU), where medical students in either condition can continue to access available mental health support as they usually would. Data collection will occur at four time-points, Time 1 (T1), pre-intervention (baseline); Time 2 (T2), post-intervention (following completion of Thumos/6 weeks after baseline for control group); Time 3 (T3), 4 months following baseline and Time 4 (T4), 9 month following baseline (see Fig 1). All elements will be conducted online, with questionnaires administered via Qualtrics and interviews/intervention sessions via online video platform. Participants will be contacted to complete the post-baseline measures via Qualtrics using email as the first point of contact and subsequent attempts to contact will be via SMS or email. All participants that complete post-baseline measures will be awarded a £10 shopping voucher per survey as compensation. Informed consent will also be taken online, with participants asked to read the information sheet and provide written informed consent via Qualtrics prior to responding to any data collection items (see S4 Appendix 2 in S4 File). A process evaluation will include medical student participants, medical educators from medical schools of participating students and the Thumos therapists.

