### Data Collection and Outcome Measures

A core online questionnaire set including measures of resilience (Brief Resilience Scale [31]), burnout (Oldenburg Burnout Inventory; OLBI [4]) confidence in coping with adverse events (CCAE [9]) depression (Patient Health Questionnaire, PHQ-9 [32]), mental health (Recovering Quality of Life-Utility Index, ReQoL-UI [33]) sickness absence and support access will be completed at T1, T2, T3 and T4 (see Tables 1 and 2). In addition, at T2 a process questionnaire will be added to this dataset (see Table 3).

**Table 1 pone.0355371.t001:** Outcome measures.

Outcome	Time	Variable definition	Effect measure
BRS (primary)	T3	BRS mean score	Adjusted mean difference/Cohen’s *d*
BRS (secondary)	T4	BRS mean score	Adjusted mean difference/Cohen’s *d*
CCAE	T3/T4	CCAE mean score	As above
OLBI	T3/T4	OLBI total and subscales	As above
PHQ-9	T3/T4	PHQ-9 total score	As above
ReQoL-UI	T3/T4	Utility score	As above
ReQoL-UI QALYs	BL-T4	QALYs area under the curve	Adjusted mean difference
Sickness absence	T3/T4	Days lost in past 4 weeks	Adjusted rate ratios with 95% CI

BRS: Brief Resilience Scale; CCAE: Confidence in Coping with Adverse Events; OLBI: Oldenburg Burnout Inventory; PHQ-9: Patient Health Questionnaire-9 item depression scale; ReQoL-UI: Recovering Quality of Life – Utility Index; QALYs: Quality-adjusted life years; BL: Baseline; T1, T2, T3, T4: Time points 1, 2, 3, and 4 (T = time)

**Table 2 pone.0355371.t002:** Outcome scoring.

Outcome	Items	Measure	Construct(s) & direction	Time points	Derived variable/scoring (incl. item response scale)
BRS (Primary)	6	Brief Resilience Scale	Resilience; higher = better	T3 [12–24 wks]	Mean of the six items after reverse scoring items 2, 4 and 6. Each item rated on a 5-point scale: 1 (Strongly disagree), 2 (Disagree), 3 (Neutral), 4 (Agree), 5 (Strongly agree).
BRS	6	Brief Resilience Scale	Resilience; higher = better	T4 [30–44 wks]	Mean of the six items after reverse scoring items 2, 4 and 6; each item rated 1 (Strongly disagree) to 5 (Strongly agree), with a “Neutral” midpoint.
CCAE	3	Confidence in Coping with Adverse Events questionnaire	Confidence coping with adverse events; higher = better	T3, T4 [12 –24, 30–44]	Mean of 3 items. Each item rated on a 4-point scale: “No – not at all”, “Unsure”, “Yes – to some extent”, “Yes – definitely”.

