OLBI (total & subscales)	16	Oldenburg Burnout Inventory	Burnout (exhaustion, disengagement); higher = worse	T3, T4 [12 –24, 30–44]	Subscale means and total mean, with reverse scoring of positively worded items according to the published scoring instructions. Each item rated on a 4-point scale: Strongly disagree, Disagree, Agree, Strongly agree.
PHQ-9	9	Patient Health Questionnaire-9	Depressive symptoms; higher = worse	T3, T4 [12 –24, 30–44]	Total score obtained by summing the nine items (range 0–27). Each item rated over the past two weeks: 0 (Not at all), 1 (Several days), 2 (More than half the days), 3 (Nearly every day).
ReQoL-UI (utility)	10	Recovering Quality of Life – Utility Index (ReQoL-UI)	Quality of life utility; higher = better	T3, T4 [12 –24, 30–44]	Utility index derived via the published ReQoL-UI algorithm, which combines the 10 mental-health items with the single physical-health item. Each mental-health item is rated on a 5-point scale from “None of the time” to “Most or all of the time” and coded 0–4 before the algorithm is applied; the physical-health item is rated from “No problems” to “Severe problems”.
ReQoL-UI QALYs	10	Recovering Quality of Life – Utility Index (ReQoL-UI)	Quality adjusted life years; higher = better	Baseline–T4	Area under the utility-time curve (derived from the utility scores above; no separate item response scale).
Sickness absence	2	Sickness absence items	Days lost last 4 weeks; higher = worse	T3, T4 [12 –24, 30–44]	Count of days lost in past 4 weeks (free numeric response).

BRS: Brief Resilience Scale; CCAE: Confidence in Coping with Adverse Events; OLBI: Oldenburg Burnout Inventory; PHQ-9: Patient Health Questionnaire-9 item depression scale; ReQoL-UI: Recovering Quality of Life – Utility Index; QALYs: Quality-adjusted life years; T3, T4: follow-up time points.

**Table 3 pone.0355371.t003:** Questionnaire assessment schedule.

	Baseline	T2 (post intervention or equivalent time)	T3 (4 month follow up)	T4 (9 month follow up)

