### Process evaluation outcomes

**To assess acceptability and how Thumos is delivered in practice through a process evaluation with users, medical educators, and providers.**

We drew upon UK Medical Research Council (MRC) guidance for process evaluations of complex interventions [36] to design a mixed-methods approach to the process evaluation.

Psychological therapist logs: Weekly logs will assess therapists’ experiences of intervention delivery, including perceived benefits, mechanisms, and challenges.Process questionnaires: Process questionnaires at T2 (post-intervention) will explore participants’ reasons for participating, and their perceptions and experiences [37]. Participants in the intervention arm will be asked about their affective attitudes to the intervention, general acceptability, perceived effectiveness, ethicality, intervention coherence and mechanisms, self-efficacy, burdens, opportunity costs, and barriers and facilitators. Participants in the control arm will be asked about their reasons for participating, and their perceptions and experiences of the study.Field notes: Researchers’ field notes will track any changes in the delivery of the intervention; enabling recording of protocol changes.Participant interviews: At T3, a randomly selected subset of participants from the intervention arm will be invited to 30-minute semi-structured interviews (n = 20) to generate information regarding intervention delivery, feasibility and acceptance, and barriers and facilitators to participation.Medical educator interviews: Once all experimental participants have completed T2 data collection, medical educators (n = 15) at schools where students have participated in the study will be interviewed to explore 1) their perceptions of the research process, and 2) perceived benefits or drawbacks of Thumos at an organisational level, 3) ways Thumos could be implemented at scale for medical students.Therapist interviews: Once all experimental participants have completed T2 data collection, all trial therapists will be invited to 30-minute semi-structured interviews exploring their experiences of delivering the intervention.

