### Safety Reporting

In this study, an adverse event (AE) will be considered any untoward medical occurrence occurring in an ACTIVATE participant whether or not related to the research procedures or intervention. An adverse reaction (AR) will be defined as an untoward and unintended response in a participant that is potentially connected to any aspect of ACTIVATE. A Serious adverse event (SAE) is defined as any adverse event that is serious and is life‑threatening or may lead to death, hospitalisation, disability, or other major medical events. A serious adverse reaction (SAR) is defined as a serious adverse event (SAE) that is related to the study. Adverse events will be recorded and reviewed by the CI, and summary reports provided to the Trial Steering committee (TSC) for review of any possible patterns.

AEs will be monitored and recorded at T2 via the inclusion of a survey question. We will also monitor them via items on the process questionnaires relating to moral and ethical concerns about the study, affective attitude towards the study (like/dislike) and experience of the study (degree of comfort experienced). All participants who indicate they may have experienced an adverse event via the survey question or report significant moral or ethical concerns, strongly disliking the study or feeling very uncomfortable will be contacted for further information and to determine whether the incident can be classed as an AE, AR, SAE or SAR.

If participants indicate during any other part of the study (e.g., during the workshops, the one-to-one call, interviews, or by contacting the study team) that an AE or SAE has occurred, they will similarly be contacted by the study team and asked to provide more information.

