Support access will be described by arm and time, not treated as an outcome or covariate. Therapy group and therapist clustering will not be modelled. Secondary and exploratory findings will be supportive, not confirmatory. We will report unadjusted and Benjamini-Hochberg false discovery rate adjusted *p* values within separate T3 and T4 secondary outcome families [38], including BRS only at T4.

Mixed models will use available outcomes, assuming data are missing at random (MAR) given observed outcomes and covariates. We will summarise missingness patterns, response rates and stated reasons for non-response, and assess predictors using logistic regression.

Sensitivity analyses will include multiple imputation under MAR, pooled using Rubin’s rules; pattern mixture adjustments subtracting 0.10, 0.20 or 0.30 points from imputed T3/T4 BRS values in Thumos only; and carrying forward the latest observed value, using baseline if no follow-up value exists. Per protocol analyses will exclude major protocol deviations and non-adherent Thumos participants and require valid T3 BRS within 12–24 weeks of baseline.

A supplementary complier average causal effect analysis of T3 BRS will use a single instrumental variables model fitted by two-stage least squares, with allocation as the instrument for minimum adherence. Both stages will adjust for baseline BRS, age, gender and medical school. All randomised participants will be included, using multiple imputation for missing outcomes. We will report the effect and 95% confidence interval, Thumos adherence proportion and first-stage partial *F* statistic.

Residual and influence diagnostics will check model assumptions. Severe non-normality or unequal residual variances will prompt sensitivity analysis using robust standard errors clustered by participant. Robustness will be judged by consistency in the T3 effect’s direction and magnitude. Scale reliability will be reported as Cronbach’s alpha and McDonald’s omega with 95% bootstrap confidence intervals. Adverse and serious adverse events will be summarised by arm, with risk differences and 95% confidence intervals but no hypothesis tests.

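### As the article describes it, adverse events are actively asked about only at T2 (about week 6 of 39), yet they are to be reported by arm with risk differences

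*Protocol article*

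**What the plan says.** **Ascertainment.** Safety Reporting in the protocol article states that "AEs will be monitored and recorded at T2 via the inclusion of a survey question". It adds process-questionnaire items on ethical concern, dislike and discomfort as a second prompt for follow-up. That questionnaire is also a T2 instrument: "at T2 a process questionnaire will be added to this dataset", and Table 3 marks it at T2 alone. For the rest of the study the article relies on participants indicating an event "during the workshops, the one-to-one call, interviews, or by contacting the study team".

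**Timing.** Trial design defines T2 as "post-intervention (following completion of Thumos/6 weeks after baseline for control group". T4 is nine months after baseline, with a window of 30 to 44 weeks in Table 2.

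**Definition and reporting.** Safety Reporting counts any adverse medical happening in a participant, related to the research or not, and sets no end date. It commits to publishing all such events. Statistical Analysis then says: "Adverse and serious adverse events will be summarised by arm, with risk differences and 95% confidence intervals but no hypothesis tests".

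**Other data to T4.** The core questionnaire set includes PHQ-9 and runs through T4 in both arms ("sickness absence and support access will be completed at T1, T2, T3 and T4"). PHQ-9 has a short recall ("Each item rated over the past two weeks"), and its stated analysis is an adjusted mean difference in the total score. Support access is to be described by arm and time point, and sickness-absence days are modelled as counts.

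**The concern.** A by-arm risk difference is only as good as the way events are found. Here the article describes one active enquiry, at about the end of the intervention, followed by some seven and a half months of passive reporting. Efficacy is judged at four months (primary) and nine months (secondary), so benefit is measured well after harm is last asked about.

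The published table could therefore show few events because few were sought, and a reader would have no way to tell. No analysis can recover late events that nobody asked about, so this concerns what is collected and cannot be left to the analysis plan.

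A second, smaller matter is that the one depression measure both arms complete to T4 is summarised as a mean. A mean can improve while a few students deteriorate markedly.

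**Working it through.** The safety text states no figure to reproduce. The planning figures used below are 220 randomised 1:1 (200 × 1.10 = 220, as stated, so 110 per arm) and dropout by T4 of 30% in Thumos and 40% in services as usual, all from Sample size calculation.

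**1. Follow-up after the active question.** T2 is at about week 6, and nine months is about 39 weeks.
- Nominal: (39 − 6)/39 = 33/39 = 85%.
- T4 window: (30 − 6)/30 = 80% to (44 − 6)/44 = 86%.

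If events arose at a constant weekly rate (an assumption), the T2 question would cover 6/39 = 15% of the time at risk. The article gives no event rates, so the number of events missed cannot be estimated.

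**2. Could the passive routes tilt the comparison?** Three of the four named contacts (workshops, call, interviews) exist only in the Thumos arm. The workshops and call come before T2, so the interviews remain: "a randomly selected subset of participants from the intervention arm will be invited to 30-minute semi-structured interviews", with n = 20 and non-completers of the intervention excluded.
- Reach: 20/110 = 18% of the arm.
- Suppose the true late event rate r is equal in both arms, the interviews find every event in those interviewed, and nobody else volunteers one. The expected addition to the risk difference is (20/110) × r: 0.9 points at r = 5% and 1.8 points at r = 10% (rates assumed). These are expected values; chance could give more or less.

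**3. What PHQ-9 could add.** Two surveys after T2, each looking back two weeks, see 4 of 33 weeks = 12% (4/38 = 11% to 4/24 = 17% across the T4 window).

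**4. How much a mean can hide.** If a fraction f worsens by d points, the mean is unchanged when the rest improve by f × d/(1 − f). Rates and sizes are assumed.

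| f | d = 5 | d = 10 |
|---|---|---|
| 5% | 0.26 | 0.53 |
| 10% | 0.56 | 1.11 |

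Among the 110 × 0.70 = 77 Thumos students expected at T4, these fractions are about 4 and 8 students.

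**5. Precision of a PHQ-9 worsening count at T4.** Expected responders are 77 and 110 × 0.60 = 66. The 95% half-width is 1.96 × √[p(1 − p)(1/77 + 1/66)], which gives 7.2 points at p = 5% and 9.9 points at p = 10%. As an example, 8/77 v 3/66 is a difference of 5.8 points (Newcombe 95% CI −3.6 to 15.1).

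**6. Can the surveys still be changed?** Recruitment runs from 16 June 2025 to 31 March 2026. Adding four months puts nominal T3 between mid-October 2025 and the end of July 2026. Adding nine months puts nominal T4 between mid-March and the end of December 2026. The last recruit's T4 window closes at 31 March 2026 + 44 weeks = 2 February 2027, which agrees with Trial Status.

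**The case against.** **The article does not say that T2 is the only time.** This stands as a limit on wording. Table 3 lists no adverse-event item at all, not even the T2 question, so its silence at T3 and T4 proves nothing. The schedule figure, the detailed protocol and the analysis plan are not shown. A reader might infer that no later question exists; the documents support only that the article describes none.

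**Asking at the end of a four-week, five-hour coaching programme is proportionate.** This is a fair defence if the aim is to catch reactions to the sessions. It fits less well with a definition that ignores relatedness and has no end date, and with a promise of by-arm risk differences.

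**Other individual-level data run to T4.** This also stands in part. Support access records when service use began, so it can place new use between surveys, which a two-week recall cannot do. Sickness absence is counted in both arms. Neither is described as a prompt for adverse-event follow-up, and seeking help may be a good sign. They soften the gap without filling it.

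**A table of PHQ-9 worsening is ordinary analysis-plan content and may be planned already.** Accepted, which is why it is secondary here. It would also be unblinded self-report from responders only, with different expected dropout by arm, so it could itself be biased.

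**The gap biases the risk difference against Thumos.** A reader might infer this from the Thumos-only contacts. Step 2 does not support more than a small expected tilt; the main effect is thin ascertainment in both arms.

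**Conclusion.** The point holds as a weakness in safety ascertainment as the article describes it. Active questioning covers about 6 of 39 weeks, and about 33 weeks (85%; 80% to 86% across the T4 window) depend on volunteered reports, while the planned by-arm risk differences carry no such qualification. It affects neither the sample size nor the efficacy analysis.

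The conclusion assumes that the article's account is complete. A later question in the full protocol would answer it.

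Two further readings are tempting and are not supported. One is that the trial has no procedure for acting on a worrying individual PHQ-9 answer: the article is silent, and such a procedure may sit in the detailed protocol. The other is that counting PHQ-9 worsening would close the gap: it sees about 12% of the time after T2 and covers depressive symptoms only.

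**What to change.** **Main change.** Ask the T2 adverse-event question of both arms in the T3 and T4 online surveys still to be sent, with a recall period reaching back to the participant's last completed survey. Report events solicited at T2 and those solicited at T3/T4 separately, with the number asked in each arm as denominators. If the question is not added, state beside the table that the risk differences rest on active ascertainment to T2 only. If the full protocol already has a later question, say so in the safety section.

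**Cost.** One question in each of two existing surveys, an amendment, and some extra follow-up contacts, since the definition is broad. Participants already past T3 or T4 are missed; how many depends on the amendment date, and with 1:1 randomisation the loss should fall about equally on both arms. Non-responders stay unasked: on the planning assumptions, 33 of 110 in Thumos and 44 of 110 in services as usual at T4.

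**Optional.** Add a descriptive by-arm count, among responders at T2, T3 and T4, of PHQ-9 worsening beyond a margin fixed before unmasking, with risk differences and intervals but no tests. Label it as unblinded self-report with differential dropout and intervals of about 7 to 10 points either side (step 5). Set it beside the support-access and sickness-absence summaries already planned. It needs no new data, only a margin and one table, and it will rarely separate the arms.

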### Data Management

All data will be kept secure and maintained in accordance with the requirements of the Data Protection Act and archived according to clinical trial GCP regulations. Personal data will be stored in encrypted, password protected formats. Identifiable personal data will be stored separately to other study data to help maintain confidentiality. Only the University of Manchester research team members will have access to the data. Only anonymised datasets will be shared with collaborators outside of the University of Manchester for the purposes of analysis.

The full dataset will be retained for up to 5 years in first instance, to enable possible follow-up studies to be conducted, should additional funding be gained. It will then be deleted, and only anonymised datasets will be retained and uploaded to the University of Manchester data archive/repository. Consent forms will also be retained during this time and destroyed at the end of this time.

### Sample size calculation

Simulations (using *powerlmm*) gave approximately 80% power with 200 participants to detect *d* = 0.50 in BRS at four months (T3; two-sided α = .05). They included repeated measurements, participant intraclass correlations of 0.30-0.50 and dropout by T4 of 30% in Thumos and 40% in services-as-usual. Adding 10% for uncertainty in these assumptions yielded a final target of N = 220 participants randomised 1:1 to Thumos or services‑as‑usual.

### Statistical Analysis

Analyses will use R and follow the statistical analysis plan (SAP; S2 File). Participants will be analysed as randomised, whatever intervention they receive. Those without follow-up outcomes will appear in flow and baseline summaries but not the primary outcome model. Treatment labels will remain masked until the primary dataset is locked and masked primary results are checked.

Recruitment, retention and adherence will be summarised as counts and percentages. Minimum adherence requires both workshops within six weeks of randomisation, with at least 75% attendance at each; the individual call is not required.

Baseline characteristics will be summarised by arm using means and standard deviations, medians and interquartile ranges, or counts and percentages, as appropriate. Absolute standardised differences above 0.20 will be highlighted, without significance testing or changes to prespecified adjustment covariates.

The primary outcome is BRS at four months (T3). A repeated measures linear mixed model will include BRS at T2–T4, with fixed effects for arm, categorical time, their interaction, baseline BRS, age, gender and medical school. We will use restricted maximum likelihood estimation and Kenward–Roger tests and confidence intervals. Within-participant covariance will be unstructured, or first-order autoregressive if the model fails to converge. The primary comparison is the adjusted T3 mean difference, Thumos minus services as usual, tested two-sided at α = .05. We will report adjusted arm means, mean differences and Cohen’s *d (using the pooled baseline standard deviation),* with 95% confidence intervals.

Continuous secondary outcomes will use the same approach, adjusted for each outcome’s baseline value. The two sickness absence counts will use separate Poisson mixed models with a log link and participant random intercept, or negative binomial models if overdispersed. We will report adjusted incidence rate ratios, marginal mean days lost by arm and absolute differences, with 95% confidence intervals. QALYs from baseline to T4 will be calculated as the area under the ReQoL-UI utility curve using linear interpolation. They will be compared using linear regression adjusted for baseline utility, age, gender and medical school, within multiple imputation.

Support access will be described by arm and time, not treated as an outcome or covariate. Therapy group and therapist clustering will not be modelled. Secondary and exploratory findings will be supportive, not confirmatory. We will report unadjusted and Benjamini-Hochberg false discovery rate adjusted *p* values within separate T3 and T4 secondary outcome families [38], including BRS only at T4.

Mixed models will use available outcomes, assuming data are missing at random (MAR) given observed outcomes and covariates. We will summarise missingness patterns, response rates and stated reasons for non-response, and assess predictors using logistic regression.

Sensitivity analyses will include multiple imputation under MAR, pooled using Rubin’s rules; pattern mixture adjustments subtracting 0.10, 0.20 or 0.30 points from imputed T3/T4 BRS values in Thumos only; and carrying forward the latest observed value, using baseline if no follow-up value exists. Per protocol analyses will exclude major protocol deviations and non-adherent Thumos participants and require valid T3 BRS within 12–24 weeks of baseline.

A supplementary complier average causal effect analysis of T3 BRS will use a single instrumental variables model fitted by two-stage least squares, with allocation as the instrument for minimum adherence. Both stages will adjust for baseline BRS, age, gender and medical school. All randomised participants will be included, using multiple imputation for missing outcomes. We will report the effect and 95% confidence interval, Thumos adherence proportion and first-stage partial *F* statistic.

Residual and influence diagnostics will check model assumptions. Severe non-normality or unequal residual variances will prompt sensitivity analysis using robust standard errors clustered by participant. Robustness will be judged by consistency in the T3 effect’s direction and magnitude. Scale reliability will be reported as Cronbach’s alpha and McDonald’s omega with 95% bootstrap confidence intervals. Adverse and serious adverse events will be summarised by arm, with risk differences and 95% confidence intervals but no hypothesis tests.

Interviews conducted as part of the process evaluation will be transcribed verbatim and analysed using Reflexive Thematic Analysis (RTA). Field notes and logs will also be analysed using RTA. RTA is a theoretically flexible approach for identifying, analysing, and reporting patterns in qualitative data and is useful for obtaining detailed insights [39]. Internal reliability of qualitative data will be strengthened through the adoption of qualitative credibility strategies such as respondent validation of transcripts, peer debriefing, and negative case analysis. Qualitative data will then be combined with quantitative data from the process questionnaires using a narrative discussion where the quantitative survey scores are presented alongside the themes produced by RTA [40]. In particular, we will follow the approach of Guetterman and Mitchell [41] who included a separate section following initial presentation of the quantitative (frequency) and qualitative (thematic) findings, labelled, ‘mixed-methods integration’. The purpose of this section will be to bring quantitative results together with relevant qualitative insights, to generate a nuanced and full picture of the dataset. This narrative discussion will be facilitated by the use of a side-by-side joint data display; a table where complementary and divergent qualitative and quantitative findings are included in columns to support the generation of complex insights [42].

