## Aims and objectives

The main purpose of the trial is to establish whether Thumos increases resilience and improves mental health in medical students.

The primary objective is:

To determine whether Thumos is superior to the control condition (services as usual; SAU) at 4-month follow-up in increasing psychological resilience in medical students.

Secondary objectives are:

1. To determine whether Thumos is superior to SAU at 9-month follow-up in increasing psychological resilience.2. To determine whether Thumos is superior to SAU at 4-month and 9-month follow-ups in the endpoints of confidence, burnout, depression, mental health, and self-reported sickness absence.3. To assess acceptability and how Thumos is delivered in practice through a process evaluation with users, medical educators, and providers

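### The mixed model imposes one baseline slope on visits from about 6 weeks to 9 months; if the baseline correlation fades over time, T4 loses some precision and, if dropout also depends on baseline, gains a small bias

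*Protocol article*

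**What the plan says.** The Statistical Analysis section of the protocol article states that "A repeated measures linear mixed model will include BRS at T2–T4". The terms of that model are then given in full: "with fixed effects for arm, categorical time, their interaction, baseline BRS, age, gender and medical school". The list names one interaction, arm with time, and a single baseline term. On covariance it says: "Within-participant covariance will be unstructured, or first-order autoregressive if the model fails to converge". The confirmatory test is at T3: "The primary comparison is the adjusted T3 mean difference, Thumos minus services as usual, tested two-sided at α = .05".

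The specification carries over to the other scales: "Continuous secondary outcomes will use the same approach", each with its own baseline value. One secondary objective concerns the latest visit directly: "To determine whether Thumos is superior to SAU at 9-month follow-up in increasing psychological resilience".

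Under Trial design, T2 is timed as "following completion of Thumos/6 weeks after baseline for control group" and the last visit as "Time 4 (T4), 9 month following baseline", which is about 39 weeks (9 × 52/12). The Sample size calculation section assumes participant ICCs of 0.30-0.50 and dropout by T4 of 30% in Thumos and 40% in services as usual (SAU).

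**The concern.** A baseline main effect without a baseline-by-time term makes the regression of outcome on baseline identical at 6 weeks, 4 months and 9 months. A baseline score often predicts a near visit better than a distant one, particularly for scales with a short recall window such as the PHQ-9. If so, the common slope settles above the true T4 slope and T4 is over-adjusted.

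The plan leaves the correlations among T2, T3 and T4 free, and its fallback structure lets them fall with lag. Only the link from baseline to each visit is held constant.

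Two things are at stake, both mainly at T4: precision, and bias if the participants still observed differ in baseline between arms. The plan relies on missingness at random given observed outcomes and covariates. That protects the estimate only if the model uses those covariates correctly at each visit.

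**Working it through.** **1. The plan's own figure.** The published simulation cannot be rerun from the article, so a two-sample normal approximation stands in for it: N = 200, d = 0.50, two-sided 0.05, full T4 dropout applied (70 and 60 observed).

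- SE = √(1/70 + 1/60) = 0.1759
- 0.50/0.1759 − 1.96 = 0.882, so power is 81.1%, against the stated figure of about 80%
- 200 × 1.10 = 220

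The design reproduces. With half the dropout (85 and 80) power is 89.4%, and with none 94.2%.

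**2. Why the slope matters.** Let b be the common slope, b4 the true T4 slope, and D the between-arm difference in mean baseline among those observed at T4. To a first approximation (the mixed model also borrows from earlier visits), the T4 estimate has expectation δ + (b4 − b)·D. Therefore:

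- bias ≈ (b4 − b)·E(D), which is zero if either factor is zero
- added variance ≈ (b − b4)²·Var(D)

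With N = 220, 110 × 0.70 = 77 and 110 × 0.60 = 66 are observed at T4, so Var(D) = 1/77 + 1/66 = 0.0281 in SD² units.

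**3. Simulation.** N = 220, T4 retention 70% and 60%, unstructured covariance, fitted with and without baseline-by-time; 1,500 trials for precision and n = 400,000 for bias. The correlations and dropout mechanisms are assumptions, because the article gives none. Age, gender and school were omitted, and estimation was by maximum likelihood. Baseline-dependent dropout means an odds ratio of 2 per SD. The variance ratio is common slope over interaction; bias is the T4 bias that the interaction removes, in SD units.

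| Baseline correlation with T2/T3/T4 | T4 variance ratio, dropout unrelated to baseline | T4 variance ratio, baseline predicts dropout equally in both arms | T4 bias, equal in both arms | T4 bias, SAU only |
|---|---|---|---|---|
| 0.50 throughout | 0.999 | 0.992 | about 0 | about 0 |
| 0.30 throughout | not run | 0.986 | about 0 | about 0 |
| 0.55/0.50/0.45 | 1.001 | 0.996 | 0.005 | 0.02 |
| 0.60/0.50/0.35 | 1.036 | 1.025 | 0.014 | 0.05 |
| 0.70/0.55/0.30 | 1.109 | 1.078 | 0.022 | 0.085 |

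With dropout unrelated to baseline, the bias removed was about zero under every pattern, despite rates of 30% and 40%.

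**4. Check against step 2.**

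- Steep decay: fitted common slope 0.598. Added variance (0.598 − 0.30)² × 0.0281 = 0.0025. Interaction-model variance 0.1539² = 0.0237. Ratio (0.0237 + 0.0025)/0.0237 = 1.11; simulated 1.109.
- Moderate decay: (0.521 − 0.35)² × 0.0281 = 0.0008; 0.1603² = 0.0257; ratio 1.03; simulated 1.036.

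**5. Other patterns.** Extending first-order autoregressive decay back to baseline (0.71/0.50/0.35) gave 6-9% extra T4 variance. A further simulation with steep decay gave 9-15%. An assumed extreme of 0.75/0.50/0.30 gave T4 standard errors of 0.1703 without and 0.1601 with the interaction. That is 6% smaller, and (0.1703/0.1601)² = 1.13, equivalent to about 13% more participants.

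**6. Consequence for T4 power.** For d = 0.5 in the 0.70/0.55/0.30 case, T4 power moves from about 87% to 89-90%.

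**7. The primary contrast.** For the patterns in the table, the T3 variance ratio was 0.99-1.01. It was about 1.02 for the autoregressive pattern, and (0.1314/0.1292)² = 1.03 for the assumed extreme. T3 bias was at most 0.003 SD with the same dropout mechanism in both arms and 0.014 SD with SAU only.

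**The case against.** The strongest reply is that nothing here is invalid. Adjusting for baseline as a main effect is legitimate and prespecified in a randomised trial. The only correlation input in the article, an ICC of 0.30-0.50, can be read as constant correlation. On that reading the common slope is correct, and the extra term costs about 1% of variance. The confirmatory test is at T3, and the article treats secondary findings as supportive. It also plans multiple imputation and models of missingness. The SAP is not shown, and an article's covariate list may omit an interaction that the SAP contains.

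Most of this stands, and it keeps the point minor. It does not remove it. The list does spell out an interaction, so the natural reading is that no other is intended. The ICC is a planning input, whereas the analysis model itself does not assume constant correlation among the follow-up visits. The planned missing-data work, as described, does not free the baseline slope.

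A reader might infer three stronger claims that the documents do not support:

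- **That the planned 30% v 40% dropout itself biases T4.** It does not. Bias also needs a slope that differs by visit and retained participants whose baseline differs by arm, and the article does not say that dropout depends on baseline.
- **That the plan wastes the equivalent of 13% of participants.** That figure belongs to one assumed extreme.
- **That bias could reach 0.15 SD.** That arose only with steep decay and baseline predicting dropout in opposite directions in the two arms, and nothing in the article suggests this.

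**Conclusion.** The point holds as a minor, conditional one. As written, one baseline slope is imposed from about 6 to 39 weeks for BRS and for all continuous secondary outcomes.

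- **Precision at T4:** no loss if baseline correlations are constant; about 0-4% of variance for mild to moderate decay; about 8-15% for steep decay.
- **Bias at T4:** about zero if dropout is unrelated to baseline; about 0.005-0.02 SD if baseline predicts dropout equally in both arms; about 0.02-0.09 SD if it does so in SAU only.
- **Primary T3 result:** practically unchanged, so this is no defect in the confirmatory analysis.

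All sizes other than the no-loss case rest on assumed correlation patterns and dropout mechanisms.

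**What to change.** Add a baseline-by-time interaction, using each outcome's own baseline value, to the primary mixed model and to every continuous secondary mixed model, leaving the other terms as they are. If the SAP already includes it, correct the article's model description to match.

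The cost is two degrees of freedom per model and no extra data. If correlations are in fact constant, about 1% of variance is lost at most. The interaction removed the T4 bias in each scenario examined where data were missing at random. Treatment labels are to stay masked until the primary dataset is locked, so the change can be prespecified before allocation is known to the analyst.
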